### Statistical analyses

Insight into the sample characterization will be provided using descriptive statistics, including measures of central tendency (mean and median) and variability (range and standard deviation). Violation of Hardy-Weinberg equilibrium will be tested by the chi-square test.

The Kolmogorov-Smirnov test will be used to verify the normal distribution of data. The comparison for between and within groups data will be analyzed using an analysis of variance (ANOVA). *Post hoc* testing will be undertaken with LSD tests.

The multivariate linear regression analysis will be performed to explore the interaction and the effect of polymorphisms on the variables: plasma levels of cytokines and physical performance, considering the genotype of each investigated.

Statistical analysis will be performed using the *Statistical Package for Social Sciences* (SPSS Inc., Chicago, IL, USA), version 17.0, and α level will be set at .05.

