## Methods/Design

### Recruitment of participants

This study is a randomized controlled trial for which community-dwellingolder women will be recruited and randomly assigned to either one of the following physical activity protocol: muscle strengthening exercises (MSE) or aerobic exercises (AE). Participants will be recruited from the community through publicity in local newspapers and community centers for older persons. The study will be conducted at the Universidade Federal de Minas Gerais, Belo Horizonte, Brazil.

After the initial evaluation, participants will be randomized into either the MSE or AE group. Randomization will be performed by means of sealed brown envelopes without identification. The researcher responsible for the evaluations will be blinded to the participants’ group.

The study was approved by the Ethics Committee of Universidade Federal de Minas Gerais (ETIC 038/2010) and all volunteers will give their written informed consent to participate, according to the principles of the Helsinki Declaration (1964).

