#### Secondary outcome measure

1. Muscle strength will be assessed using a Biodex® System 3 Pro isokinetic dynamometer (Biodex Medical Systems Inc., Shirley, NY,USA). This instrument has been accepted as the “gold standard” for assessment of muscular performance [37]. The muscle groups assessed will be the knee joint extensors and flexors of the dominant limb at angular speeds of 60° and 180° in concentric contractions, with 5 and 15 repetitions respectively, at intervals of 30 seconds between each velocity. All procedures will be performed according to the assessment protocol suggested by the manufacturer, such as positioning of the volunteer, calibration, correction for gravity, familiarization and strong verbal encouragement. Variables chosen for analysis are work normalized by body mass (%) at 60°, and Power at 180°.

2. Aerobic capacity, as measured by the 6-Minute Walk Test (6MWT). The 6MWT has been used in patients who have different disorders, such as neurological, cardiothoracic, infant or rheumatologic dysfunctions, and its correlation with maximum aerobic capacity is considered to be satisfactory [38,39]. Data related to systemic blood pressure, heart rate and subjective perception of effort using the Borg scale will be recorded.

3. Geriatric Depression Scale (GDS) is a screen for the presence of depression in older people. It comprises 15 individual questions; the cut-off-points will be 5/6 (non-case/case) [40,41].

4. The level of stress will be assessed by the 14-item Perceived Stress Scale validated for Brazilian older persons. This scale assesses three factors considered to be keys in the experience of stress: how the subject evaluates his life as unpredictable, uncontrollable and overloaded [42].

The salivary cortisol level will be measured as an objective measurement of stress [42]. The salivary cortisol level will be collected with cortisol specific Salivette tubes (Sarstedt.Salivette-swab). The dosage of the salivary levels will be performed using the ELISA method (*Salimetrics*).

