### Sample size

Based on the multivariate linear regression analysis that will be performed in this study to explore the SNP influence on the effects of exercise on plasma levels of cytokines and onephysical performance, 140 older adults need to be included, considering the sample calculation of (10 x (K + 1), where K is the number of explanatory variables of the model. The explanatory variables are age, anthropometric measurements (Body Mass Index and Waist Circumference), physical activity level, presence of depression and stress levels (Perceived Stress Scale and salivary cortisol), TNF-α rs1800629 (AA + AG versus GG) , IL6 rs1800795 (GG versus CC + GC) , IL10 rs1800896 (GG versus AA + AG), genes polymorphisms.

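### The baseline value of the outcome is not a covariate in the ANOVA or in the listed regression model, and the time point of covariates that are also secondary outcomes is not fixed

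*Protocol article*

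**What the plan says.** Statistical analyses gives two methods. For the groups: "The comparison for between and within groups data will be analyzed using an analysis of variance (ANOVA", followed by LSD post hoc tests. For the genetic question there is a linear regression of cytokine levels and physical performance, meant to explore both the interaction and the effect of the polymorphisms. It does not say whether the response is the follow-up value or the change.

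The regressors appear under Sample size: "The explanatory variables are age, anthropometric measurements (Body Mass Index and Waist Circumference), physical activity level", then "presence of depression and stress levels (Perceived Stress Scale and salivary cortisol", then three SNPs, each coded in two levels. The baseline value of the outcome is not on the list. Nor is the randomised arm, unless physical activity level stands for it. No time point is given for the covariates.

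On timing, Recruitment of participants says: "After the initial evaluation, participants will be randomized into either the MSE or AE group". The SE protocol section says that women are reassessed once the 30 sessions are complete.

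Secondary outcome measure includes the Geriatric Depression Scale and the Perceived Stress Scale, and adds: "The salivary cortisol level will be measured as an objective measurement of stress". All three therefore appear both as outcomes and as regressors.

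**The concern.** The baseline value is usually the strongest available predictor of the follow-up value of a cytokine or a timed walking test. A model without it leaves explainable variance in the error term and leaves chance baseline imbalance in the estimate. The primary objective is an interaction between SNPs and the exercise effect, so precision matters.

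Interpretation is also at stake. Both arms exercise, and the Discussion reports that women homozygous for the IL-6 G allele already have high IL-6. If the regression response is the follow-up level with no baseline term, a SNP coefficient mixes that standing difference with a genotype-dependent response to training.

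The second issue is the double role of depression, perceived stress and cortisol. Measured before randomisation, they are ordinary covariates. Measured at follow-up, they may themselves have been changed by the exercise programme, and conditioning on them would distort the randomised comparison.

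**Working it through.** **The plan's own figure.** The sample size is stated as "140 older adults need to be included", from a rule of 10 × (K + 1).

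- Named variables: age, BMI, waist circumference, physical activity level, depression, Perceived Stress Scale, cortisol and three SNPs, so K = 10.
- 10 × (10 + 1) = 110, not 140.
- 140 / 10 − 1 = 13, so the rule implies three terms that are not named.

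The figure is not reproduced from the list. That mismatch is a separate matter. Here it means that the list may be incomplete.

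**Is a baseline value available?** Evaluation precedes randomisation, women are reassessed after the programme, and the ANOVA has a within-group part. The article does not itemise the initial evaluation, but these three statements together imply that the outcomes are measured at both times.

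**Precision.** Assume equal SD (set to 1) at both times and pre-post correlation r. The residual variances for the arm comparison are:

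- follow-up only: 1
- change score, equivalent to the group-by-time test: 2(1 − r)
- ANCOVA: 1 − r²

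So ANCOVA / change = (1 − r²) / [2(1 − r)] = (1 + r) / 2, and ANCOVA / follow-up only = 1 − r².

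| r (assumed) | ANCOVA / change | 140 by ANCOVA is worth, by change | ANCOVA / follow-up only | 140 by ANCOVA is worth, by follow-up only |
|---|---|---|---|---|
| 0.5 | 0.75 | 140 / 0.75 = 187 | 0.75 | 140 / 0.75 = 187 |
| 0.8 | 0.90 | 140 / 0.90 = 156 | 0.36 | 140 / 0.36 = 389 |

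The change columns fit the ANOVA. The follow-up-only columns apply only to a regression of the follow-up level with no baseline term.

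**The same in power.** Assume 70 per arm, two-sided 0.05 and a true difference of 0.4 SD. Follow-up only gives 0.66 at every r.

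| r (assumed) | Change | ANCOVA |
|---|---|---|
| 0.3 | 0.52 | 0.70 |
| 0.5 | 0.66 | 0.78 |
| 0.7 | 0.86 | 0.91 |

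**Covariates that are also outcomes.** Suppose the arms differ by a SD at follow-up in stress, depression or cortisol, and one SD of that variable shifts the study outcome by b SD. Conditioning on the follow-up value then removes a × b from the arm effect. For assumed a = 0.2 to 0.4 and b = 0.1 to 0.3, this is 0.2 × 0.1 = 0.02 SD up to 0.4 × 0.3 = 0.12 SD. With pre-randomisation values, a is zero apart from chance, and no such bias arises.

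**Does the corrected model fit the plan's own rule?**

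- Ten listed + arm + three arm-by-SNP terms + baseline: K = 15, N = 160.
- The same, if physical activity level means the arm: K = 14, N = 150.
- The K = 15 model without depression, Perceived Stress Scale and cortisol: K = 12, N = 130.

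**The case against.** Several stronger readings are tempting and are not supported.

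- **That the ANOVA ignores baseline.** A comparison between and within groups, with assessments before and after the programme, reads as group-by-time. Baseline is then the first time level, and the interaction test equals a change-score comparison, which is unbiased under randomisation. Preferring ANCOVA is a gain in efficiency, not the correction of an error, and the follow-up-only figures do not belong to this analysis.
- **That the regression is biased because it adjusts for outcomes.** Nothing says that follow-up values will be used. A variable can be a secondary outcome and, measured before randomisation, a proper covariate. A condensed article may also leave the time point to a fuller document. What stands is that the text permits either reading, and only one is safe.
- **That physical activity level is meaningless among sedentary women.** Sedentary is defined by a threshold of frequency and duration. Women below it can still differ, and the term may even denote the arm.
- **That the omission is certain.** The rule implies 13 terms and 10 are named, so a baseline term could be among the missing three. If the regression response is change, baseline is already used in part. Still, the list is introduced as the model's explanatory variables, and baseline is not on it.

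Two points limit the remedy. The regression is also meant to estimate the effect of polymorphisms on cytokine level, and adjusting for the baseline cytokine would absorb much of that effect. In a model with other covariates, the relevant r is the partial correlation, so the gains above may be somewhat overstated.

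**Conclusion.** The point holds as an improvement in precision and clarity. As written, neither the ANOVA nor the listed regression model has the baseline outcome as a covariate, although the design provides it. Against the group-by-time ANOVA, ANCOVA removes 10% to 25% of the variance for an assumed r of 0.8 down to 0.5. The saving over follow-up only, 25% to 64% over the same range of r, is conditional on a regression response that the article does not specify. All these sizes rest on an assumed correlation and equal variances at the two times.

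The bias from depression, stress and cortisol is conditional as well. It arises if follow-up values enter the model and not if baseline values do. The article should close off the first possibility, but it does not commit to it.

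**What to change.** 1. For the exercise effect and the arm-by-SNP interaction, state one model per outcome: follow-up value regressed on arm, baseline value of the same outcome, the three SNPs and the arm-by-SNP terms.
2. If the SNP effect on cytokine level itself is of interest, estimate it separately without baseline-cytokine adjustment, for example on the baseline levels.
3. State that every other covariate, including depression, perceived stress, cortisol and physical activity level, is the value measured before randomisation. Say whether physical activity level means the arm. Once these covariates are fixed at baseline, keeping or removing them is a matter of choice.

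**Cost.** The change is one of analysis wording, with no new data. Under the 10 × (K + 1) rule, keeping all ten listed variables beside the new terms gives 160 (150 if physical activity level is the arm), above 140. Leaving out depression, perceived stress and cortisol gives 130. The sponsor should therefore either shorten the list or say that the rule of thumb does not bind the final model.

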## Discussion

The elevation of the plasma inflammatory cytokine levels has as its main consequences sarcopenia [6,18,19], reduction of function and independence of the older adult. We have previously demonstrated a weak to moderate negative correlation between high plasma levels of IL-6 and sTNFR-1, and reduced muscle strength and physical performance in older women [3,4].

Within this context, physical exercise has been presented as one of the most effective strategies to influence both an improvement in physical performance and a decrease in plasma levels of inflammatory markers in the older adult [7,24,29]. However, even though physical exercise has been widely performed in clinical practice, there is no consensus on which type of exercise and what clinical parameters are the most influential on the inflammatory markers. Thus, the results of this clinical trial could contribute to the standardization and management of clinical practice related to prevention and treatment of functional changes in the older adult.

A series of evidence suggests that the SNP could affect the production of cytokines, also influencing physical, cognitive and behavioral performance, and muscle strength in the olderadult [18,19,22]. We have recently investigated the effect of the -174 G/C polymorphism of the IL-6 gene on the plasma IL-6 levels in both community dwelling and institutionalized older women. Homozygotes women for the G allele showed high IL-6 levels, and an interaction between polymorphism and housing conditions (community/institution) was observed, with a higher effect of GG genotype on IL-6 levels in the institutionalized women [45].

The genes involved in the regulation of the chronic inflammatory process can contribute not only to the individual variability of cytokine production and physical performance in the older adult, but also to the response of these variables to physical exercise. Still, it is important to note that the evaluation of a single cytokine genotype without considering its interaction with other genotypes from different biological markers could lead us to misinterpretations, as their combined action could result in different effects. Therefore, analyzing and understanding the influence of genetic factors on the effects of different exercise protocols as proposed by this study may contribute to the development of new perspectives on preventive and therapeutic approaches in physical therapy and in general management of the older patient. This trial was designed to be reproducible in both research and clinical environments.

## Abbreviations

10MWT: 10-Meter Walk Test;1RM: one repetition maximum;6MWT: 6-Minute Walk Test;AE: aerobic exercises;EDTA: ethylenediaminetetraacetic acid;ELISA: Enzyme Linked Immunosorbant Assay;GDS: Geriatric Depression Scale;IL-10: interleukin-10;IL-6: interleukin-6;IL-8: interleukin-;MSE: muscle strengthening exercises;SNP: single nucleotide polymorphism;sTNFR: soluble TNF receptors;TNF-α: tumor necrosis factor alpha;TUG: Timed Up and Go.
